#### Case management

Case management sessions, led by the same provider leading the group therapy portion of DBT-J, are held every other week for up to 30 min to assist in coordinating connection to and care between the treatment team, legal services, and social services within the VA system and/or VCLI’s community. For example, for VCLI with active substance use, sessions may facilitate connection to local 12-step programs to support efforts toward sobriety. For VCLI facing financial difficulties, sessions may include referral to VA benefits advisors. Where possible, providers coach clients through applying skills learned in group therapy sessions (e.g., problem solving) to resolve case-management difficulties. Motivational interviewing strategies are also used throughout these sessions to promote sustained connection to care. Informed by SDM, case management is tailored to the client’s unique needs and balances foci on resolving factors contributing to criminogenic risk (e.g., substance use) with those prioritized by the Veteran (e.g., financial instability).

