### DBT-J and suicide risk

The structure and content of DBT-J directly targets overlapping risk factors for antisocial behavior and suicide by: (a) building and strengthening behavioral skills for observing limits, mindfulness, emotion regulation, goal directedness, interpersonal effectiveness, and relapse prevention; and (b) facilitating connection to services and resources that reinforce use of adaptive skills. In early DBT-J trials, one-third of participating Veterans had a history of attempting suicide, and one-third were experiencing suicidal ideation upon program admission [20, 35]. Although analyses were underpowered to detect statistically significant effects, Veterans who completed the program experienced, on average, moderately sized (*d* = 0.30–0.88) improvements in multiple suicide risk factors across the course of treatment, including substance use, psychological distress, and quality of life [35].

DBT-J providers utilize a formal suicide risk assessment and management protocol designed for Veteran samples and VA contexts [36] to facilitate ongoing risk monitoring and efficient, therapeutic responses to acute changes in VCLI suicide risk. Comprehensive suicide risk assessments prior to program entry provide an initial conceptualization of VCLI acute and chronic risk for suicide (i.e., immediate risk and propensity toward increases in immediate risk, respectively). Ongoing monitoring of risk and protective factors is then used throughout the course of the VCLI’s participation in DBT-J to guide suicide risk assessment and management. Notable changes in risk and/or protective factors (e.g., increase in psychosocial stress, decrease in social support) prompt more structured suicide risk assessment and management strategies as necessary to promote VCLI safety. Various VA-based supports, such as those offered by the Veterans Crisis Line, VA Suicide Prevention Coordinators, and other behavioral health providers, are also integrated into suicide risk management efforts to promote effective, sustained risk mitigation.

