## Randomized clinical trial

A multisite randomized Stage III clinical trial will be conducted to assess the efficacy of DBT-J. A total of 200 Veterans will be recruited across three regions in the U.S. (VA VISNs 2, 19, and 21) over three years (2024–2026; anticipated date of recruitment completion, June 30, 2026). Random assignment, stratified by region and generated using an electronic random number generator, will be used to assign participating Veterans to DBT-J or a supportive group therapy condition. Assignment will be completed immediately after enrollment and available only to the PI and individuals involved in intervention delivery; assignment is masked from individuals involved in assessment completion. Veterans will receive 16 weeks of assigned intervention followed by a 36-week observation period. To inform evaluations of treatment efficacy, participants will also complete assessments in 8-week intervals during the intervention period beginning at baseline and 12-week intervals during the follow-up period (6 times total). See Table 2. All protocols were developed in accordance with the Declaration of Helsinki and have been approved by the VA Central Institutional Review Board; protocols and analysis plans are pre-registered through clinicaltrials.gov (NCT05974553, registered July 26, 2023). All participants will provide informed consent prior to participation. To preserve participant confidentiality, individual participant data will not be shared with anyone outside of the immediate research team.

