### Data analysis plan

Analyses will employ an alpha of 0.05, use two-tailed tests, and be completed using SPSS and/or the R Computing Environment. Preliminary analyses will include computing descriptive statistics and inspecting data to determine whether data transformations are needed, statistical assumptions are met, and psychometric properties of each scale are sound. Multiple imputation will be used for transient missing data. Because participants who dropout of the protocol may be qualitatively distinct from protocol completers (e.g., due to differences in motivation, legal requirements, etc.), analyses will also include a sensitivity analysis by comparing the full “intent-to-treat” sample against protocol completers. Potential confounders, including duration of outside treatment services received during the intervention period, will be compared across conditions and included as covariates in subsequent analyses if significantly related to study outcomes.

Primary and secondary analyses will be investigated using analyses of covariance to compare participants in the DBT-J and supportive group conditions on primary and secondary continuous treatment targets at post-treatment after controlling for baseline scores. Poisson regression with robust error variance will similarly be used to compare DBT-J and comparison conditions on dichotomous secondary treatment targets (suicide attempt during study period and criminal recidivism during study period). The DBT-J condition will be considered superior to the supportive group condition if participants in the DBT-J condition demonstrate statistically superior scores on either primary treatment target at post-treatment. The DBT-J intervention will be considered efficacious if results suggest (a) superiority to the supportive group condition and (b) clinically significant change in primary efficacy outcomes from baseline to post-treatment among DBT-J participants [67].

To support exploratory analyses comparing efficacy of DBT-J programming across VCLI subgroups, DBT-J participants will be coded according to most recent offense type (violent or nonviolent), presence of a substance use disorder, and presence of a severe mental illness (i.e., mood or psychotic disorder). Multivariate analyses of covariance will be used with subgroup membership included as predictor variables, LS/CMI and IPF post-treatment scores included as dependent variables, and LS/CMI and IPF baseline scores included as covariates.

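### The covariate rule can bring outside services received after randomisation, which DBT-J is designed to change, into the primary ANCOVA

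*Protocol article*

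**What the plan says.** The protocol article's Data analysis plan has a rule for covariates that names one variable: "Potential confounders, including duration of outside treatment services received during the intervention period, will be compared across conditions and included as covariates". The condition for entry comes at the end of the sentence, where such variables are "included as covariates in subsequent analyses if significantly related to study outcomes". The next paragraph gives the main efficacy analysis, an ANCOVA with this task: "compare participants in the DBT-J and supportive group conditions on primary and secondary continuous treatment targets at post-treatment after controlling for baseline scores". It adds a Poisson regression for the dichotomous secondary outcomes. The rule is not restricted to baseline variables, nor is adjustment for services confined to a secondary or sensitivity role.

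Elsewhere the article describes how DBT-J bears on services. Under Case management, the biweekly sessions are there "to assist in coordinating connection to and care between the treatment team, legal services, and social services within the VA system" or in the community. Under DBT-J and suicide risk, one of two stated ways in which the programme acts is "facilitating connection to services and resources that reinforce use of adaptive skills". Under Study conditions, individualised case management is listed among the DBT-J-specific elements that the supportive group will not contain. Both arms may continue care with outside providers.

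**The concern.** A confounder of a randomised comparison has to precede assignment. Service use in weeks 0 to 16 follows it, and the article itself describes a path from assignment through service connection to outcome. Adjusting for a variable on that path removes the part of the DBT-J effect that runs through it. If unmeasured need or motivation drives both service use and outcome, adjustment also opens a non-causal link between arm and outcome.

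At stake is the quantity that the primary test estimates. The trial could miss an effect that exists or report one that does not, and the adjusted result alone would not show which. A second, lesser problem is that selecting covariates by their observed relation to outcome leaves the primary model open until outcome data are seen, and it could give different models for the LS/CMI and the IPF.

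**Working it through.** **1. The plan's own figure.** Inputs from Justification of sample size: d = 0.50, alpha 0.025, 80% power, 20% dropout; two-tailed tests from the Data analysis plan. Normal approximation: n = 2(2.241 + 0.842)² / 0.50² = 76.04, so 77 per arm. The exact t-test gives 78. The plan states 80, at which power is 0.815. Enrolment: 80 / 0.80 = 100 per arm, 200 in total. The figure is reproduced and this point does not affect it.

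**2. Formula.** Let a be the arm difference in services (in SD) and β the within-arm coefficient of outcome on services, given the baseline score. Then

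adjusted effect = total effect − a × β.

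There is no distortion if a = 0 or β = 0. The documents give neither value, so everything below rests on assumed ranges. Positive values favour DBT-J.

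**3. Services as a pure mediator, total effect 0.50.** Here β is the effect of services on outcome. Example: 0.50 − 0.5 × 0.2 = 0.40. The plan's rule was also simulated: 80 per arm, baseline score in the model, services added if correlated with outcome at p < 0.05, two-sided alpha 0.025, 3,000 trials per row.

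| a | β | 0.50 − aβ | Covariate selected | Mean estimate under the rule | Power under the rule |
|---|---|---|---|---|---|
| 0.3 | 0.2 | 0.44 | 74% | 0.45 | 0.73 |
| 0.3 | 0.3 | 0.41 | 96% | 0.42 | 0.68 |
| 0.3 | 0.4 | 0.38 | 100% | 0.38 | 0.62 |
| 0.5 | 0.2 | 0.40 | 80% | 0.41 | 0.62 |
| 0.5 | 0.3 | 0.35 | 98% | 0.35 | 0.50 |
| 0.5 | 0.4 | 0.30 | 100% | 0.30 | 0.39 |
| 0.8 | 0.2 | 0.34 | 87% | 0.35 | 0.43 |
| 0.8 | 0.3 | 0.26 | 99% | 0.26 | 0.24 |
| 0.8 | 0.4 | 0.18 | 100% | 0.18 | 0.14 |

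Without services in the model, the estimate stays at 0.50 and power at about 0.81 to 0.82. With a = 0 the rule also leaves the estimate at about 0.50.

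**4. No true effect, services inert, an unmeasured factor driving both.** Let the factor load g on services and h on outcome (unit variances), and let the baseline score load λ on the factor. Then

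β = g h (1 − λ²) / (1 − g² λ²), and bias = −a × β.

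Take a = 0.5 and loadings of equal size. The table gives the size of the bias.

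| Loadings g, h | λ = 0 | λ = 0.5 | λ = 0.7 | λ = 0.8 |
|---|---|---|---|---|
| 0.5 | 0.125 | 0.10 | 0.07 | 0.05 |
| 0.3 | 0.045 | 0.03 | 0.02 | 0.02 |

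Example: 0.25 × 0.75 / 0.9375 = 0.20, and 0.5 × 0.20 = 0.10. The sign depends on the factor. If it raises service use and worsens outcome (severity), the bias favours DBT-J; if it raises service use and improves outcome (motivation), the bias goes against DBT-J.

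Allowing for the selection step, with loadings of 0.5 and λ = 0, the simulated bias at a = 0.5 is about 0.11 in either direction, with type I error of 0.06 to 0.07 instead of 0.025. Across a = 0.3 to 0.8, type I error is 0.04 to 0.12. These error rates are upper-end illustrations, because λ = 0 means that the baseline score carries no information on the factor.

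**5. Both mechanisms together.** With a = 0.5, a service effect of 0.2 and severity loadings of 0.5 (λ = 0), β = 0.2 − 0.25 = −0.05. The adjusted effect is 0.50 + 0.025 = 0.525, so the two biases nearly cancel.

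**The case against.** The strongest reply is that the bias is conditional. The covariate must be selected, and assignment must shift it. The only service-use measure that the article describes is the nature and duration of VA-based mental health care from chart review, whereas its case management examples are 12-step programmes and benefits advice, which that measure may miss. This stands as a limit on size: the arm difference could be small. It does not rescue the rule, because a zero difference would mean that assignment left service use unchanged, contrary to the purpose given for case management.

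It is also fair that the authors want to examine outside services. Need for continued research says that the earlier pre-post studies could not separate DBT-J from outside care. The randomised comparator now answers that question. Looking at services remains legitimate in a sensitivity or mediation analysis, so a ban on any adjustment would go too far.

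A reader might infer three stronger points that the documents do not support:

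- That the result would be biased in a known direction, or more so the better DBT-J links Veterans to care. Steps 4 and 5 show either sign, and near-cancellation when both mechanisms act.
- That leaving the stratification factor, region, out of the stated model is an error. A condensed article can leave that to the full protocol or SAP.
- That selection by significance is itself the source of bias. For true baseline covariates it is mainly a weakness of prespecification; the bias comes from the post-randomisation variable.

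**Conclusion.** The concern holds in a conditional form. As written, the plan allows a variable that arises after randomisation, and that DBT-J is designed to change, into the primary and secondary efficacy models. When it is selected and the arms differ on it, the ANCOVA does not estimate the total effect of assignment.

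Confidence is high that the flaw exists. Its size and direction cannot be derived from the documents. Under the assumptions in step 3, a true 0.50 is estimated at about 0.45 down to 0.18. Under those in step 4, with no true effect and a 0.5 SD arm difference, the bias is about 0.02 to 0.12 SD either way, and smaller the better the baseline score captures severity. Because the rule reaches the primary test, it should be changed before analysis.

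**What to change.** In the Data analysis plan:

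- Remove service use during the intervention period, and the outcome-significance rule, from the primary and secondary efficacy models.
- Limit covariates to prespecified baseline variables: the baseline score and, as a low-cost addition, the region stratum.
- Report outside services by arm. Keep any adjustment for them to an analysis labelled as sensitivity or mediation, with its assumptions stated.

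The cost is analysis wording, plus two degrees of freedom if the three regions are added. No new data are needed, and the sample size stays at 80 evaluable per arm and 200 enrolled.

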Both conditions will prioritize supporting the needs and experiences of VCLIs, have a closed-group format, and have an enrollment cap of 8 members per group, allowing Veterans to build meaningful relationships with other group members throughout the treatment period. Both will also be delivered via telehealth to ensure program accessibility regardless of participants’ housing status, transportation barriers, or physical location. All interventions will be provided as an adjunctive service, allowing Veterans to continue care with outside providers throughout their participation in the clinical trial. Information about study participation will be documented in VA electronic medical records to inform outside treatment planning and ensure continuity of care. Following completion of the 16-week intervention period, Veterans will continue treatment as usual with their outside providers for the 32-week observation period.

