#### Justification of sample size

A priori power analysis was used to determine an appropriate sample size to support primary aim analyses. Informed by results of previously collected pilot data [20, 35], we anticipated at least a moderately-sized difference across conditions in primary efficacy outcomes at post-treatment. Power analysis results suggested at least 80 participants per condition (160 total) are needed to achieve 80% power to reject the null hypothesis of equal means when the population mean difference is *d* = 0.50 and α = 0.025 (to adjust for multiple comparisons). After adjusting for an anticipated dropout rate of 20%, 100 participants per condition (200 total) are required to achieve necessary statistical power.

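### Both arms are treated in closed therapy groups, but the ANCOVA and the sample size assume independent participants: type I error is inflated if outcomes correlate within groups, and 80% power is not shown

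*Protocol article*

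**What the plan says.** Under Randomized clinical trial, Veterans are randomised individually, stratified by region. Under Study conditions, the article says that both arms "have a closed-group format, and have an enrollment cap of 8 members per group", so that members can form relationships over the treatment period. The comparator is built around alliance among members and clinicians. Under Case management, the provider who leads a DBT-J group also leads its members' individual sessions.

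The Data analysis plan specifies "analyses of covariance to compare participants in the DBT-J and supportive group conditions on primary and secondary continuous treatment targets at post-treatment", controlling for baseline. It names no therapy-group or provider effect and no variance clustered by group. The Poisson models for dichotomous outcomes use robust error variance, but not by group. The exploratory MANCOVA and repeated-measures ANOVA have no such term either.

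Justification of sample size states that "at least 80 participants per condition (160 total) are needed to achieve 80% power". The effect assumed there is d = 0.50, tested at an alpha of 0.025 chosen to allow for more than one comparison. The evaluable number is then raised for 20% dropout to 100 randomised per arm. No ICC, mean group size, design effect or baseline correlation is given.

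**The concern.** Members of a closed group share a clinician, a group climate and each other for 16 weeks, and both treatments are meant to work partly through that contact. Individual randomisation does not undo correlation that arises afterwards within groups. If outcomes correlate within groups, the variance of an arm mean exceeds what ordinary ANCOVA assumes. The standard error is then too small and the test rejects too often.

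The same ANCOVA serves both primary outcomes and all continuous secondary outcomes, and superiority rests on it. The power calculation has the matching gap. This is not detail left to an unseen analysis plan: the article names the model and gives the full sample-size arithmetic, and both assume independence.

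**Working it through.** **Inputs from the article.** d = 0.50; alpha 0.025 two-sided; 80 evaluable per arm; 20% dropout; 100 randomised per arm; group cap 8.

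**Assumptions, not in the article.** ICC 0.01 to 0.10; groups filled to the cap; baseline correlation r = 0.5 where credited.

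**1. The plan's own figure.** A two-sample t-test with independent observations needs 78 per arm for 80% power. With 80 per arm the power is 81.5%. Then 80 / 0.8 = 100. The stated size is therefore the independent-participants result plus dropout, with no allowance for a design effect.

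**2. Number and size of groups.** 100 / 8 = 12.5, so at least 13 groups per arm, or 2 × 13 − 2 = 24 group-level degrees of freedom (df). Analysed per group: m = 8 × 0.8 = 6.4.

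**3. Formulas.**
- Design effect: DE = 1 + (m − 1) × ICC.
- Effective n per arm = 80 / DE.
- Standard errors grow by √DE.
- Type I error of a test that ignores clustering: 2 × [1 − Φ(z / √DE)], with z = 1.960 (nominal 5%) or 2.241 (nominal 2.5%).
- Power: noncentral t with noncentrality 0.50 × √(effective n / 2). With baseline credited, effective n is divided by 1 − r² = 0.75.

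**4. Results with m = 6.4.**

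| ICC | DE | √DE | Effective n per arm | Type I, nominal 5% | Type I, nominal 2.5% | Power, participant-level df | Power, 24 group-level df | Power, r = 0.5, participant-level df |
|---|---|---|---|---|---|---|---|---|
| 0.01 | 1.054 | 1.03 | 75.9 | 5.6% | 2.9% | 79% | 75% | 90% |
| 0.02 | 1.108 | 1.05 | 72.2 | 6.3% | 3.3% | 77% | 73% | 88% |
| 0.05 | 1.27 | 1.13 | 63.0 | 8.2% | 4.7% | 70% | 66% | 83% |
| 0.10 | 1.54 | 1.24 | 51.9 | 11.4% | 7.1% | 61% | 57% | 75% |

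Example, ICC 0.05: DE = 1 + 5.4 × 0.05 = 1.27; 80 / 1.27 = 63.0; 1.960 / √1.27 = 1.739, which gives a two-sided 8.2%.

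With r = 0.5 and 24 group-level df, power is 85%, 80% and 71% at ICC 0.02, 0.05 and 0.10.

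**5. Simulation check.** Simulating the ANCOVA without a group term, with 13 groups of 6 per arm, 20,000 runs and r = 0.5, gives type I error of 6.2%, 7.7% and 11.0% at nominal 5%, and 3.5%, 4.2% and 6.8% at nominal 2.5%, for ICC 0.02, 0.05 and 0.10. The inflation remains although baseline is in the model.

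**6. Smaller groups.** If groups average 5 enrolled, so 4 analysed, ICC 0.05 gives DE = 1 + 3 × 0.05 = 1.15. Type I error is then 6.8% and 3.7%, and power without baseline credit is about 75%.

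Both nominal levels are shown because the Data analysis plan and the sample-size section state different alphas. That is a separate matter and adds nothing to the size of this point.

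**The case against.** The harm is conditional. It needs a within-group ICC above 0 for the outcome in question after baseline adjustment, and the article gives none. At ICC 0.01 the effect is small: 5.6% against 5%, 2.9% against 2.5%, and power of 79%. The figure of 8 is a cap, not a mean, so 13 groups per arm is a minimum and 6.4 analysed per group is an upper value under 20% dropout. All of this stands, and it is why the sizes are given as a range.

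A reader might infer that p-values will certainly be too small, or that every continuous comparison will exceed its nominal level. The documents do not support that, because they contain no evidence on the ICC for any outcome.

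A reader might also infer that the trial is underpowered. That goes too far. The sample size is for an unadjusted comparison, whereas the analysis controls for baseline, and this gain was not credited. With r = 0.5, power on participant-level df exceeds 80% at ICC 0.01, 0.02 and 0.05. The omitted gain may offset the omitted design effect; no baseline correlation is stated, so neither outcome can be shown.

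Finally, this is a condensed article, and analysis plans are said to be registered elsewhere. That limits certainty about the final model. It does not supply a clustering term to the model stated here, and the general promise to check statistical assumptions does not commit to one.

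**Conclusion.** The point holds in conditional form. The stated ANCOVA and the stated sample size both treat participants as independent, although both arms are delivered in closed groups. If the ICC is above 0, type I error is inflated: about 5.6% to 11% at nominal 5% and about 2.9% to 7% at nominal 2.5%, for an assumed ICC of 0.01 to 0.10 with groups filled to the cap, and less with smaller groups. The type I half is the firmer one, since baseline adjustment does not cure it. On power, the supportable statement is that the quoted 80% is not shown for this design: about 79% to 61% without baseline credit on participant-level df, about 75% to 57% on group-level df, and about 90% to 75% with r = 0.5 on participant-level df.

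**What to change.** Before outcomes are analysed:

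- Replace the ANCOVA with a linear mixed model containing condition, baseline score, region (the randomisation stratum) and a random intercept for therapy group in both arms, with Kenward-Roger or Satterthwaite df.
- In the Poisson models, cluster the robust errors by therapy group and apply a small-sample correction, because full groups would give only about 26 clusters.
- Keep n = 200 and restate power over a declared range of ICC, mean group size and baseline correlation, using group-level df.

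Group membership is known from delivery, so no new data are needed, and recruitment and treatment do not change. The cost is wider intervals, with standard errors roughly 3% to 24% larger over the assumed range (√1.054 to √1.54), and a less favourable stated power. If the ICC proves close to zero, the loss is small.

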## Veterans with criminal-legal involvement

VCLI are a high-risk, high-need population overrepresented in behavioral healthcare settings within the U.S. Department of Veterans Affairs (VA), a federal entity that provides healthcare, social services (e.g., housing support), benefits (e.g., financial compensation for service-related injuries), and funeral services to eligible military Veterans (VA; [5]. In 2023, the suicide rate for VCLI was approximately 145 per 100,000, over four times that of Veterans overall and over eight times that of civilian adults [6]. Results of a recent meta-analysis suggest 81% of VCLI experience a mental health condition and 69% experience a substance use disorder; rates of mood, trauma-related, and personality disorders appear particularly overrepresented in this population [7]. In comparison to Veterans without a history of criminal-legal involvement, VCLI are also more likely to engage in suicidal, violent, and otherwise aggressive behaviors and to experience homelessness, occupational instability, and poor community integration [8–11]. These challenges may contribute to difficulties with sustained service engagement by increasing transience, introducing demands for complex care coordination, and prompting crisis intervention that can interfere with care continuity (e.g., inpatient hospital stays).

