### Participants

Veterans will be recruited via referral from local mental health providers, VA VJP Specialists, treatment court providers, and local Veteran service organizations and via self-referral through mail-based recruitment. To be considered for inclusion, Veterans must be aged 18 + ; able to provide consent (i.e., have capacity to understand the study’s purpose, risk, and benefits and make an informed decision about participation); and have a recent history of criminal-legal involvement, defined as criminal arrest, order of protection, or incarceration within two years prior to participation and/or supervision by probation or parole at the time of enrollment. Exclusion criteria include limited English proficiency; inability to tolerate group therapy format; concurrent enrollment in another clinical trial; concurrent enrollment in interventions based in the RNR model (e.g., MRT) or DBT; and prior participation in DBT-J. Using similar inclusion/exclusion criteria, prior studies have yielded VCLI samples that are predominantly male with notable heterogeneity in race, ethnicity, age, presenting mental health concerns, and criminal-legal history [20, 35]. To maximize generalizability of results to the heterogeneous population of VCLIs, no inclusion/exclusion criteria related to psychopathology and/or VA eligibility will be used. VCLI experience a range of psychosocial needs [7], and many are not eligible for comprehensive VA care due to discharge status or other barriers [46]. Previous trials have successfully enrolled VCLIs across the psychosocial need spectrum, including those with active suicidal ideation, homelessness, psychotic disorders, and severe substance use [20, 35], suggesting feasibility of this flexibility in inclusion/exclusion criteria.

Consistent with previous DBT-J trials [20, 35], we anticipate a dropout rate of 20% during the intervention period, resulting in a final sample size of approximately 160 at post-treatment. Participants are considered to have dropped out of participation after missing four consecutive group sessions. There are otherwise no attendance requirements for participation.

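### The robust Poisson test fixed for suicide attempt gives false significance when exactly one arm has no attempts; how often depends on an attempt rate the protocol does not give

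*Protocol article*

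**What the plan says.** The protocol article's Data analysis plan assigns one method to both binary secondary outcomes: "Poisson regression with robust error variance will similarly be used to compare DBT-J and comparison conditions on dichotomous secondary treatment targets". The outcomes are named in the same sentence: "suicide attempt during study period and criminal recidivism during study period". The general settings are also fixed: "Analyses will employ an alpha of 0.05, use two-tailed tests, and be completed using SPSS and/or the R Computing Environment".

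No other method is named for an outcome with few or no events. The nearest safeguard is the preliminary look at descriptive statistics and assumptions, which does not say what to do if an arm is empty.

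The section Justification of sample size sets the numbers: "100 participants per condition (200 total) are required to achieve necessary statistical power". They are derived for the primary means, and nothing is calculated for suicide attempt. No section states an expected attempt rate during the study. The introduction gives a death rate ("the suicide rate for VCLI was approximately 145 per 100,000"), and the section on DBT-J and suicide risk gives the share of earlier participants with a past attempt or with ideation at admission. Neither is an attempt incidence.

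**The concern.** Robust Poisson regression is a standard way to estimate a risk ratio for a binary outcome, but it needs at least one event in each arm. With about 100 people per arm followed for about a year, an arm with no suicide attempts is a realistic possibility. The stated test then does not become uninformative, as one would want. It becomes extremely significant, because the point estimate diverges and the robust standard error does not grow with it.

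Suicide-related behaviour is in the secondary aim and in the rationale for the trial. Followed literally, the plan could report a highly significant benefit or harm on suicide attempts from one or two events, with a rate ratio near zero or infinity and a meaningless confidence interval.

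**Working it through.** **Inputs.** From the protocol: 100 per arm randomised; 80 per arm after the anticipated loss ("we anticipate a dropout rate of 20% during the intervention period"); two-sided alpha 0.05; robust Poisson. Assumed, because the documents do not give it: the attempt risk over the study period, equal in both arms.

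**The plan's own figure.** The plan says "at least 80 participants per condition (160 total) are needed to achieve 80% power to reject the null hypothesis of equal means", at d = 0.50 and alpha 0.025. A two-sample calculation gives 77 (normal) or 78 (t) per arm, and power at 80 per arm is 0.82 (normal) or 0.81 (t). Then 160 / 0.8 = 200. The figure reproduces, but it concerns the primary means only.

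**Why the test fails.** Let μ be the fitted mean in an arm of n people. That arm's contribution to the robust variance of the log rate ratio is Σ(y − μ)² / (Σμ)².

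- Arm with b events: μ = b/n, and the contribution is 1/b − 1/n.
- Arm with no events: the fit stops at a tiny μ > 0, and the contribution is nμ² / (nμ)² = 1/n.
- Sum: 1/b − 1/n + 1/n = 1/b, so the robust SE is √(1/b) however far the estimate has run.
- The model-based variance for the empty arm is 1/(nμ), which grows without limit as it should.

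**Fitted in R, 100 per arm (glm, HC0 variance).** Each fit reported convergence without a warning.

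| Attempts | log RR | robust SE | robust Wald p | Fisher p |
|---|---|---|---|---|
| 0 v 1 | −17.7 | 1.00 | <0.001 | 1.00 |
| 0 v 2 | −18.4 | 0.71 | <0.001 | 0.50 |
| 0 v 4 | −18.1 | 0.50 | <0.001 | 0.12 |

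The model-based SE was in the thousands (p about 1.0). Statsmodels gave log RR −20.4 and robust SE 1.00 for 0 v 1. Where the estimate stops depends on the convergence tolerance, so the exact p-value means nothing; only p<0.001 is stable.

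**How often, with no true difference.** With risk p and q = (1 − p)ⁿ, the chance that exactly one arm is empty is 2q(1 − q). Example at p = 1%, n = 100: q = 0.99¹⁰⁰ = 0.366, so 2 × 0.366 × 0.634 = 0.464. Adding the tables with events in both arms, tested with SE = √(1/a − 1/n + 1/b − 1/n), gives the total rejection probability at nominal 0.05:

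| Assumed risk | One arm empty, n = 100 / 80 | Robust Poisson rejects, 100 / 80 | Fisher rejects, 100 / 80 |
|---|---|---|---|
| 0.5% | 0.478 / 0.442 | 0.478 / 0.442 | <0.001 / <0.001 |
| 1% | 0.4641 / 0.4945 | 0.4641 / 0.4945 | <0.001 / <0.001 |
| 2% | 0.230 / 0.318 | 0.231 / 0.319 | 0.005 / 0.002 |
| 3% | 0.091 / 0.160 | 0.094 / 0.161 | 0.011 / 0.007 |
| 4% | 0.033 / 0.073 | 0.043 / 0.079 | 0.017 / 0.012 |
| 5% | 0.012 / 0.033 | 0.029 / 0.045 | 0.021 / 0.016 |
| 10% | 0.0001 / 0.0004 | 0.041 / 0.037 | 0.029 / 0.028 |

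The first column peaks at exactly one half, where q = 0.5: a risk of 0.69% with 100 per arm or 0.86% with 80. Simulation of 4,000 null trials per scenario agreed (share with p<0.001 at 1% risk: 0.457 with 100 per arm, 0.503 with 80). Adding a covariate hardly changed it (0.456 and 0.499).

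**The case against.** **A fallback for sparse data is normally left to the statistical analysis plan, which is not shown.** That is fair as far as an omission goes. But the article positively assigns this test to this outcome, and the assigned test gives a wrong answer in a foreseeable situation. An unseen plan may already deal with it.

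**The attempt rate is unknown.** This stands, and it limits the claim. A reader might infer that about half of null trials would show a false effect. The documents do not support that: one half is the worst point of an assumed range. Past attempts in one-third of earlier participants, ideation at admission in one-third, and no psychopathology exclusions leave a rate of 4–5% or more open, and there the test is at or below its nominal level. The death rate in the introduction cannot stand in for an attempt rate.

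**An analyst would notice.** Probably: a zero count would show in the descriptive statistics, and a rate ratio of the order of 10⁻⁸ is visibly degenerate. The tabulated error rates therefore describe the plan followed literally. But choosing another test after seeing counts by arm is the post hoc decision that pre-specification should prevent.

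**SPSS may behave differently.** It was not run and may issue a warning. The plan equally allows R, which gave none.

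**Nothing primary depends on it.** Correct. Superiority and efficacy are defined on the primary targets alone.

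**Conclusion.** The concern holds in a limited form. For suicide attempt, the stated test fails whenever exactly one arm has no events, and reports p<0.001 from as little as 0 versus 1. Its false-positive rate ranges from nearly one half at assumed risks of 0.5–1%, through 23–32% at 2% and 9–16% at 3%, to at or below nominal from about 4% with 100 per arm or 5% with 80. This rests on equal true risks, the planned arm sizes and literal use of the robust Wald test.

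Two further readings are not supported. Robust Poisson is not shown to be unsuitable for binary outcomes in general; for recidivism it is adequate if events are common. And the trial's main conclusion is not at risk, since this is a secondary outcome outside the superiority rule. If both arms have no attempts, there is no false significance; the ratio simply cannot be estimated.

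**What to change.** Add one sentence to the Data analysis plan: if either arm has zero or very few suicide attempts (with the number fixed in advance), the arms will be compared by an exact method (Fisher's or Barnard's test, with an exact confidence interval for the risk difference) or by a penalised, Firth-type model. Event counts will be reported by arm in every case. Keep robust Poisson otherwise, and apply the same fallback to recidivism.

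A conditional rule is enough. Suppose Fisher's test replaces robust Poisson only when an arm is empty. Total rejection cannot then exceed the robust test's rejections with events in both arms plus the chance of an empty arm, or plus Fisher's overall rejections if that is smaller. At 5% risk with 100 per arm this is 0.0175 + 0.0118 = 0.029; at 10% it is 0.0411 + 0.0001 = 0.041. It stays below 0.05 at every rate examined, from 0.145% to 10%.

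The cost is one sentence and no new data. The exact test is slightly conservative and cannot carry the covariates or the multiple imputation that the plan provides for, so the sentence should say how missing outcomes are counted. A penalised model could keep a covariate, though so few events would support little adjustment.
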